### Acupuncture interventions

Eligible participants will be randomly allocated into the VA or SA group at a 1:1 ratio via the web-based response system of the Central Randomisation System for Clinical Research. Stratified randomization will be applied, with age (35 years) as the stratification factor. Unblinding will not be required during the study as it will not have clinical relevance to treatment decisions. The randomization plan will be generated using the “Proc plan” procedure in SAS 9.3 statistical software (SAS Institute Inc., Cary, NC, USA), and all related parameters set during the randomization process will be stored in a blinded database. When eligible participants are enrolled, the randomization number will be assigned by the responsible personnel or researcher through phone or online access to the central randomization system. The random distribution cards will contain random numbers, serial numbers, and groups, packed in opaque numbered envelopes. The envelope will be unsealed following study enrolment. Owing to the particularity of acupuncture research, it is difficult to blind the acupuncture operators. As such, fake acupuncture devices and separate treatment rooms will be used for each patient to blind them as much as possible. Moreover, the “three separations strategy” will be strictly adhered to by researchers, operators, and statisticians throughout the research process. Efficacy evaluation, data analysis, and statistics will be completed by third parties blinded to the groupings.

Acupuncture or sham acupuncture will be administered by certified acupuncturists and have received prior standardized training in operation. Both groups chose the same acupoints, which is same to our previous protocol (26), including two sets of acupoints (group A and group B) comprising 14 selected points will be manually applied to patients, alternately, starting with group A (number of needle insertions per patients per session: 6 or 20). Based on the prior studies, the “Fertility-Menstruation Regulating Thirteen Acupuncture Points” was chosen for this trial. Acupoints of group A include Baihui (GV20), Shenting (GV24), bilateral Benshen (GB13), Zhongwan (CV12), bilateral Tianshu (ST25), Guanyuan (CV4), bilateral Zigong (EX- CA1), bilateral Dahe (KI12), bilateral Zusanli (ST36), bilateral Sanyinjiao (SP6) and bilateral Taichong (LR3). Group B consists of three acupoints: bilateral Shenshu (BL23), bilateral Zhongliao (BL33) and bilateral Taixi (KI3). The locations of each of the acupoints according to the WHO Standard Acupuncture Point Locations in the Western Pacific Region are listed in **Table 1**.

**Table 1 T1:** Locations of acupoints.

Acupoint	Location	Insert angle	Insert depth
GV20	On the head, 5 proportional bone (skeletal) cun (B-cun) superior to the anterior harline, on the anterior median line	0°	10–20 mm
GV24	On the head, 0.5 B-cun superior to the anterior hairline, on the anterior median line	15°	10–20 mm
GB13	On the head, 0.5 B-cun superior to the anterior hairline, 3 B-cun lateral to the anterior median line	15°	10–20 mm
CV12	On the upper abdomen, 4 B-cun superior to the centre of the umbilicus, on the anterior median line	90°	30–40 mm
ST25	On the upper abdomen, 2 B-cun lateral to the centre of the umbilicus	90°	30–40 mm
CV4	On the lower abdomen, 3 B-cun inferior to the centre of the umbilicus, on the anterior median line	90°	30–40 mm
EX-CA1	On the lower abdomen, at the same level as Zhongji (CV3), 3 B-cun lateral to the anterior median line	90°	30–40 mm
KI12	On the lower abdomen, 4 B-cun inferior to the centre of the umbilicus, 0.5 B-cun lateral to the anterior median line	90°	30–40 mm
ST36	On the anterior aspect of the leg, on the line connecting Dubi (ST35) with jiexi (ST41), 6 B-cun inferior to ST35	90°	30–40 mm
SP6	On the tibial aspect of the leg, posterior to the medial border of the tibia, 3 B-cun superior to the prominence of the medial malleolus	90°	30–40 mm
LR3	On the dorsum of the foot, between the first and second metatarsal bones, in the depression distal to the junction of the bases of the two bones, over the dorsalis pedis artery	90° [obliquely towards Yongquan (KI1)]	10–20 mm
BL23	In the lumbar region, at the same level as the inferior border of the spinous process of the second lumbar vertebra(L2),1.5 B-cun lateral to the posterior median line	90°	30–40 mm
BL33	In the sacral region, in the third posterior sacral foramen	90°	60–70 mm
KI3	On the posteromedial aspect of the ankle, in the depression between the prominence of the medial malleolus and the calcaneal tendon	90°	30–40 mm

The patients were asked to lie on their backs or stomach (depends on group A or B) in a quiet position, exposed to acupuncture. For VA group, after 75% alcohol disinfection, the Hwato^®^ (Huatuo brand made in Suzhou Medical Appliance Factory, Jiangsu, China) disposable needle (Φ=0.25*25 mm, Φ=0.25*40 mm, Φ=0.30*75 mm) is used in conjunction with the Park Sham Acupuncture Device (PSD, DongBang acupuncture company) (30). Expose the tip of the needle, apply a suitable needle insertion method, and attach the park device to the skin. Depending on the muscular layer depth of the acupuncture points, we adjusted the needle insertion depth until the patient experienced the “deqi” sensation. Needle manipulation techniques such as lifting, thrusting or twirling will be applied to promote ‘deqi’ (a sensation experienced by patients at the acupoint location, characterized by soreness, numbness, heaviness, and distention, etc). Acupuncture needles for VA will be inserted perpendicularly into a depth of 10–20 mm for GV20, GV24 and GB13, obliquely towards Yongquan (KI1) into a depth of 10–20 mm for LR3, deeply into a depth of 60–70 mm into the third posterior sacral foramina for BL33, and perpendicularly into a depth of 30–40 mm for the remaining acupoints. Needle retention time will last for 20 min per session, once every other day, 3 sessions a week for 12 weeks, totaling 36 treatment sessions.

The SA group will receive a non-inserted acupuncture using the sham needle supported by the PSD. This needle has a retractable needle shaft and a blunt tip, they could not penetrate the skin (33). We gently placed the sham needle and PSD on the skin. The sham needle is then left no more manipulated to avoid any further physiological effects, thereby minimizing the potential for additional effects (34). The acupoints is same to the VA group. At the end of the treatment, the acupuncturist also used a dry cotton ball to press the acupoints so that patients could feel the withdrawal of ‘real’ needles (35).

At the conclusion of the trial, all participants were asked to complete a blinding assessment questionnaire containing the following question: “Which group do you believe you were assigned to during the study?” The response options were: A) VA (treatment group), B) SA (control group), or C) Uncertain. This assessment served three primary purposes: First, to quantify blinding efficacy by calculating the percentage of correct versus incorrect guesses. Second, to validate whether the sham acupuncture procedures had successfully masked group allocation. Finally, to assess any potential bias in self-reported outcomes, particularly for psychological scales.

During the trial period, all participants were explicitly instructed to refrain from any additional interventions, including moxibustion, cupping, and herbal remedies, that could potentially influence the study outcomes.

### Clinical outcome measurement

The AFC will be measured via transvaginal ultrasonography on days 2–5 of the menstrual cycle. AFC, along with serum levels of basal FSH and AMH, will be assessed at three time points: baseline (week 0), post-treatment (week 12), and 12-week follow-up (week 24).

The neuro-psychological test such as SAS, SDS, and SRSS will be used for clinical assessments at three time points: baseline (week 0), post-treatment (week 12), and 12-week follow-up (week 24).

The time points for each test in two group is listed in **Table 2**.

**Table 2 T2:** Time points for each test in two groups .

Measurements	Baseline		12 weeks		24 weeks	
	DOR	HC	DOR	HC	DOR	HC
AFC, FSH, AMH	✓	✓	✓		✓	
AFC	✓		✓			
SAS, SDS, and SRSS	✓	✓	✓		✓	
MRI	✓	✓	✓			

Diminished ovarian reserve, DOR; healthy control, HC; anti-Müllerian hormone, AMH; antral follicle count, AFC; follicle-stimulating hormone, FSH; self-rating anxiety scale, SAS; self-rating depression scale, SDS; self-rating scale of sleep, SRSS; magnetic resonance imaging, fMRI.

### fMRI data acquisition

All DOR patients received two separate resting-state fMRI scanning, before and after the 12 weeks acupuncture treatment course, respectively. The healthy controls participated only in one resting-state scanning as baseline control. For all participants, fMRI scanning should be done at least 3 day away from their menstrual period.

In this study, 3.0 T MRI scanner (Siemens, Sonata, Germany) at the Sir Run Shaw Hospital, was used to perform cranial scans on all subjects. (1) T1-weighted imaging (T1WI): horizontal axis position, TR = 600 ms, TE = 10 ms, slice thickness = 4 mm, slice gap = 1.5 mm, field-of-view (FOV) = 240 mm × 240 mm, matrix = 256×256. (2) Resting-state fMRI sequence and parameters: acquired with gradient echo-echo planar imaging (GRE-EPI) sequence, TR = 2000 ms, TE = 30 ms, slice thickness = 4 mm, slice gap = 1.2 mm, FOV = 220 mm × 220 mm, matrix = 64 × 64, flip angle = 90°, 200 time points in total, 35 slices scanned continuously. The entire brain will be scanned, and during the procedure, participants will be instructed to lie supine with their eyes open, while being asked to refrain from focusing on any specific thoughts.

### Incidence of adverse events

All adverse events (AEs) will be recorded and assessed. The principal investigator and ethics committee will determine whether the participants should withdraw from the trial. AEs contain any unfavorable but mild signs, symptoms, or feelings. AEs will be recorded in detail in the case report forms (CRFs). Acupuncture is a minimally invasive treatment, and its adverse events cannot be completely avoided.

### Sample size calculation

This is an exploratory study, and according to the highly cited experimental fMRI studies had a single group of participants and these studies had median sample size of 12, the sample size of 12 cases in each group and 20 to 30 cases has become the “minimum requirement” and most choices for acupuncture imaging confirmatory studies. We have expanded the sample size to 21 cases per group (36).

### Demographic and clinical data analyses

Demographic and clinical outcome analyses will be conducted using SPSS 22.0 software. In the cross-sectional study, two-sample t-tests and Chi-square tests will be employed to compare baseline characteristics between the DOR patient group and HCs. In the longitudinal study, paired t-tests will be used to compare changes in clinical symptoms (SAS, SDS, and SRSS scores) and laboratory test results (AFC, FSH, and AMH) within each group before and after treatment. Subsequently, a two-way analysis of variance (ANOVA), with time as the within-subject factor, will be applied to examine differences in clinical symptoms between the VA and SA groups before and after treatment. A *p*-value of < 0.05 will be considered statistically significant.

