## Abstract

Diminished ovarian reserve (DOR) is characterized by a decrease in the quantity and quality of oocytes, leading to reduced chances of natural conception and a poorer response to fertility treatments. Along with these reproductive challenges, DOR often causes psychological symptoms such as depression, anxiety, and sleep disturbances, which negatively affect overall well-being and quality of life. Acupuncture has been proposed as a promising complementary therapy for DOR, but the mechanisms through which it exerts its effects are not yet fully understood. This study aims to investigate the effects of acupuncture on ovarian function, psychological well-being, and the central nervous system in women with DOR. We will recruit 42 women with DOR and 21 healthy controls (HCs), randomly assigning DOR patients to receive either verum acupuncture (VA) or sham acupuncture (SA) for 12 weeks. Ovarian function will be assessed using Anti-Müllerian hormone (AMH), antral follicle count (AFC), and follicle-stimulating hormone (FSH). Psychological well-being will be evaluated using the Self-Rating Anxiety Scale (SAS), Self-Rating Depression Scale (SDS), and Self-Rating Scale of Sleep (SRSS). To explore the neurological effects, resting-state functional connectivity (rsFC) of the hypothalamus will be assessed using functional magnetic resonance imaging (fMRI). This research aims to clarify how acupuncture affects the central nervous system, hormonal regulation, and ovarian function in women with DOR. The findings may provide valuable insights for developing evidence-based acupuncture protocols that can improve both reproductive outcomes and quality of life for women with DOR.

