## Materials and methods

### Study design

This study will consist of two experiments: a cross-sectional experiment and a longitudinal experiment (**Figure 1**). The cross-sectional experiment will examine brain functional connectivity (FC) in patients with DOR by comparing seed-based FC between DOR patients and healthy controls (HCs). The longitudinal experiment will investigate the clinical efficacy of acupuncture and its underlying neurological mechanisms by comparing FC before and after treatment. Additionally, we will compare the differences in FC and clinical symptoms, such as ovarian function, anxiety, depression, and sleep disturbances, between the VA and SA groups following treatment. Finally, we plan to analyze the relationship between changes in FC and clinical symptoms. This will allow us to investigate whether acupuncture can modulate hypothalamic FC and subsequently improve clinical symptoms in DOR patients. The longitudinal acupuncture experiment was approved by the Ethics Committee of Sir Run Shaw Hospital Zhejiang University School of Medicine (2025YL0012) and submitted to the International Traditional Medicine Clinical Trial Registry (ITMCTR2025000576). All participants will be provided written informed consent before the initiation of any study procedures. The study adhered to the CONSORT guidelines for reporting

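### The design section promises a VA-versus-SA comparison of ovarian function, but the analysis section names AMH, AFC and FSH only in within-arm paired t-tests

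*Protocol article*

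**What the plan says.** The Abstract makes ovarian function a main aim and defines it: "Ovarian function will be assessed using Anti-Müllerian hormone (AMH), antral follicle count (AFC), and follicle-stimulating hormone (FSH"). Under Acupuncture interventions, DOR patients are "randomly allocated into the VA or SA group at a 1:1 ratio".

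The Study design section commits to comparing "clinical symptoms, such as ovarian function, anxiety, depression, and sleep disturbances, between the VA and SA groups following treatment". Here ovarian function is one of the clinical symptoms.

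The section on demographic and clinical data analyses first states that "paired t-tests will be used to compare changes in clinical symptoms (SAS, SDS, and SRSS scores) and laboratory test results (AFC, FSH, and AMH"), and it places these tests "within each group before and after treatment". The scales and the laboratory results are two separate classes in that sentence. The next sentence introduces a two-way ANOVA with time as the within-subject factor, which "will be applied to examine differences in clinical symptoms between the VA and SA groups before and after treatment". Laboratory results are not mentioned there. A *p*-"value of < 0.05 will be considered statistically significant".

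**The concern.** The analysis section sorts outcomes into two classes and then applies the between-arm test to one of them by name. On its own wording, the only longitudinal test that names AMH, AFC or FSH is a before-after test inside each arm. That does not deliver the VA-versus-SA comparison of ovarian function in the Study design section.

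A within-arm change mixes any treatment effect with time trend, placebo response and regression to the mean. Nor does a significant result in VA beside a non-significant one in SA show that the arms differ. The Introduction faults an earlier protocol for not allowing for the placebo effect, and the sham arm is there to deal with that. Reading the ovarian markers within arms would bring the same weakness back for a headline outcome.

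**Working it through.** **1. The texts side by side.**

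| Section | Meaning of clinical symptoms | Comparison | Are AMH, AFC, FSH covered? |
|---|---|---|---|
| Study design | Ovarian function, anxiety, depression, sleep | VA versus SA | Yes, through ovarian function |
| Clinical data analyses, paired tests | SAS, SDS, SRSS; laboratory results listed apart | Before versus after, each arm | Yes, by name |
| Clinical data analyses, ANOVA | Term repeated without a gloss | VA versus SA | Not named; excluded if the gloss just given applies |

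For the connectivity maps, the MRI data preprocessing section names both the within-group paired test and the between-group ANOVA. The ovarian markers have no equivalent statement in the analysis section.

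**2. Two paired tests read against each other.** Inputs from the article: 21 per arm and a 0.05 level. Assumptions: two-sided tests, normal change scores, and the same true change δ in both arms (in SDs of the change score; the article gives none).

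Each paired statistic follows a noncentral t with 20 df and noncentrality δ√21; the critical value is 2.086. Let U be the chance of a significant improvement and S the chance of significance in either direction. The arms are independent, so

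P(VA improves significantly, SA not significant) = U × (1 − S).

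- δ = 0: 0.025 × 0.95 = 0.024
- δ = 0.45: noncentrality 0.45 × 4.583 = 2.06, U ≈ S ≈ 0.501, and 0.501 × 0.499 = 0.250

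| Common change δ | VA paired test significant | VA improves, SA not significant | Between-arm test significant (100,000 simulations) |
|---|---|---|---|
| 0 | 5.0% | 2.4% | 5.1% |
| 0.2 | 14.1% | 11.9% | 5.0% |
| 0.4 | 41.5% | 24.3% | 4.9% |
| 0.45 | 50.1% | 25.0% | 5.0% |
| 0.5 | 58.7% | 24.2% | 5.1% |
| 0.8 | 93.6% | 6.0% | 5.0% |

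The product p(1 − p) cannot exceed 0.25, so 25% is the ceiling. The between-arm test is a t-test on change, which equals the group-by-time term when there are two time points.

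**3. Regression to the mean in AMH.** Entry requires AMH below 1.2 ng/ml. The simulation has no treatment effect, 21 patients, selection on a noisy screening value and then a re-measurement. The log-scale SD of 0.7, the medians and the reliabilities are all assumptions. The figures are rates of falsely significant improvement by the paired test, against a nominal 2.5%.

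| Baseline value used | Median AMH of those screened (ng/ml) | Reliability 0.95 | 0.90 | 0.80 |
|---|---|---|---|---|
| Fresh week-0 sample | any tried | 2–3% | 2–3% | 2–3% |
| Screening value | 0.5–0.7 | 3–4% | 4–6% | 5–8% |
| Screening value | 1.2–2.0 | about 8–15% | about 12–25% | about 20–48% |

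A between-arm test of change on data with the screening value as baseline rejects in about 5% of trials. AFC was not simulated. FSH has no numeric entry cut-off, so the selection argument is not shown for it.

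**The case against.** The strongest reply is that the between-arm comparison is already planned. The Study design section counts ovarian function among the clinical symptoms, the ANOVA is applied to clinical symptoms, and so the ANOVA covers AMH, AFC and FSH. The study is labelled exploratory, and the full analysis plan, not shown, may list the outcomes for each model.

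Much of this stands. A reader might infer from the analysis section that the ovarian markers are tested only within arms and that the sham arm plays no part in the ovarian conclusion. The document does not support that: a VA-versus-SA comparison is promised, and the paired tests are run in SA too. Nor does any section say that an efficacy claim will rest on a paired test, or on significance in one arm and not the other. The 25% is a maximum for a reading that the article does not prescribe.

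It would also go too far to say that AMH and AFC must rise on re-measurement. The article does not say whether the week-0 value is the screening value. If it is a fresh sample, the paired test is at its nominal rate.

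What does not stand is the view that nothing needs changing. The analysis section does more than leave a detail open: it assigns outcomes to tests, and its assignment disagrees with the Study design section. An exploratory label does not turn a before-after *p*-value into a comparison with sham.

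**Conclusion.** The finding holds as a contradiction between two sections, and it should be resolved before analysis because it decides whether a headline outcome gets a randomised comparison.

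If the analysis section is followed literally and the two paired tests are read against each other, the risk of a spurious contrast favouring VA is 2.4% to 25% per marker, depending on an assumed common change, with a between-arm test near 5% throughout. The added risk from regression to the mean in AMH is not determined by the article. It runs from none, with a fresh week-0 sample, to a false-improvement rate of nearly 50% at the adverse end: screening value as baseline, reliability 0.80 and a screened median of 2.0 ng/ml. That upper figure is a bound under stated assumptions and not an estimate for this trial.

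**What to change.** In the section on demographic and clinical data analyses, state that:

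- AMH, AFC and FSH are compared between VA and SA, either by the group-by-time term of the planned ANOVA or, preferably, by a baseline-adjusted model at week 12;
- the between-arm difference is reported with its 95% CI, and any conclusion on ovarian function rests on it;
- the within-arm paired t-tests are descriptive.

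Use clinical symptoms with one meaning in both sections. The minimum repair is to add the laboratory results to the ANOVA sentence. Log scales for AMH and FSH and a stated rank for week 24 are optional.

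The cost is wording only: no new data, visits or participants. The fix does not add power. With 21 per arm, 80% power needs a between-arm difference of about √(2/21) × (1.960 + 0.842) = 0.86 SD of the change score (0.89 by the t distribution), so the interval should carry the interpretation.

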There are two limitations to consider. (a) Due to limited funding, it’s a single-center study, we are unable to conduct multi-center, large-scale trials, which may reduce the generalizability and strength of the evidence. However, we will focus on enhancing patient compliance to optimize the quality of the research. (b) The purpose of this study is to investigate the underlying mechanism of this acupuncture point scheme, and therefore, SA was selected to minimize the placebo effect and enhance the scientific rigor of the experimental design to use as a control group. Given the urgent needs of DOR patients, SA may not produce significant clinical effects, as a result, there may be a higher dropout/loss-to-follow-up rate. In future studies, conventional treatments such as HRT or hormone-modulating therapy (HMT) could be incorporated to fulfill ethical considerations and provide additional comparative insights.

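### The before/after ANOVA for verum versus sham gives up precision by leaving out baseline adjustment and the age stratum, and as worded does not cover week 24

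*Protocol article*

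**What the plan says.** All places are in the protocol article.

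- **Demographic and clinical data analyses** sets paired t-tests "within each group before and after treatment", followed by "a two-way analysis of variance (ANOVA), with time as the within-subject factor, will be applied to examine differences in clinical symptoms". The contrast that this model serves is worded as "between the VA and SA groups before and after treatment". No covariate is named. The same section separates "clinical symptoms (SAS, SDS, and SRSS scores) and laboratory test results (AFC, FSH, and AMH"), and the ANOVA sentence mentions only the former. Study design, by contrast, counts ovarian function among the clinical symptoms.
- **Acupuncture interventions**: "Stratified randomization will be applied, with age (35 years) as the stratification factor".
- **Clinical outcome measurement** schedules the ovarian markers and the three scales at "baseline (week 0), post-treatment (week 12), and 12-week follow-up (week 24"). Table 2 agrees, except that AFC appears twice, the second time without week 24.
- **MRI data preprocessing** uses age as a covariate, but only in the imaging comparison of patients with healthy controls.
- **Sample size calculation**: "We have expanded the sample size to 21 cases per group", set by precedent in an exploratory study.
- **Discussion** (limitations): because SA may not bring significant clinical effects, "there may be a higher dropout/loss-to-follow-up rate". No rate is given.

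**The concern.** The article names the model that will compare the arms, so the model can be judged on its merits. In a trial of 42 patients, information already collected should be used fully, and three pieces are not:

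- **Baseline** enters only as a level of the time factor, not as a covariate.
- **Age stratum** was considered important enough to stratify on, yet it is absent from the VA–SA model.
- **Week 24** is collected but has no stated test, so how it is analysed could be decided after the data are seen.

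Dropout adds to this. Paired t-tests and a classical repeated-measures ANOVA use only women with every value in the comparison, while the article itself expects extra loss because of the sham control.

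**Working it through.** **Inputs.** From the document: 21 per arm (42/2), 1:1 allocation, significance level 0.05, stratification at age 35, outcomes at weeks 0, 12 and 24. Assumed, because the document gives no value: two-sided testing, 80% power, equal SD at both visits, correlation ρ of 0.3 to 0.7, a true difference of 0.8 SD for the power figures, and the age effects and dropout rates below.

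**The plan's own figure.** The 21 per group rests on precedent, with no effect size, SD or power, so there is no calculation to reproduce.

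**1. Baseline.** With two times, the group-by-time F test is the square of the t-test on change scores. In units of SD²:

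- change-score variance: 2(1−ρ)
- baseline-adjusted variance: 1−ρ²
- ratio: (1−ρ²)/[2(1−ρ)] = (1+ρ)/2

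Noncentral t, 21 per arm:

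| ρ | Variance ratio | Equivalent n per arm (21/ratio) | Detectable difference: change → adjusted | Power at 0.8 SD: change → adjusted |
|---|---|---|---|---|
| 0.3 | 0.65 | 32.3 | 1.05 → 0.85 SD | 57% → 75% |
| 0.5 | 0.75 | 28.0 | 0.89 → 0.77 SD | 72% → 83% |
| 0.7 | 0.85 | 24.7 | 0.69 → 0.63 SD | 90% → 94% |

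Hand check at ρ = 0.5: 0.886 × √0.75 = 0.767. Spending two degrees of freedom on covariates moves this only to 0.768.

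**2. Age stratum.** Simulation of the change-score test (20,000 replicates, 42 women, arms balanced within strata of 20 and 22). With age effects on change of 0.5, 1.0 and 1.5 SD, the true type I error is about 4.3%, 2.9% and 1.4%. With age in the model it stays near 5%. Omitting age therefore makes the test conservative and does not create false positives.

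**3. Week 24.** Clinical outcome measurement labels week 12 as post-treatment and week 24 as follow-up. The analysis section speaks only of before and after treatment. No stated analysis clearly reaches week 24, and the imaging analyses cannot, since Table 2 has no scan then.

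**4. Dropout (assumed rates, ρ = 0.5).** If only SA loses women, the detectable difference for the planned test rises from 0.89 SD (21 v 21) to 0.91 (21 v 19) and 0.96 (21 v 16). Power at 0.8 SD falls from 72% to 69%, 67% and 63% with 19, 17 and 15 SA women. At 10%, 20% and 30% SA loss, the SA mean change shifts as follows:

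- If women with the worst baseline leave: by about 0.10, 0.18 and 0.25 SD. Baseline adjustment removes this.
- If women with the worst change leave: by about 0.19, 0.35 and 0.50 SD. Adjustment leaves about 0.15, 0.26 and 0.37 SD, so it removes only about a quarter.

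No outcome visit lies between weeks 0 and 12. A woman lost before week 12 has no response value in a model of weeks 12 and 24, just as she has no pair in the ANOVA.

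**The case against.** The best defence is that the planned test is valid: under full follow-up, group-by-time estimates the treatment effect without bias, and the study calls itself exploratory. Covariates and missing-data rules often sit in an analysis plan that is not shown, and "after treatment" could be read to include week 24.

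The validity point stands and limits the severity. The rest stands only in part. The article does not leave the model open: it names one, and that one is inefficient. A three-level time factor is possible, but the visit labels point to week 12 alone. Even on the wider reading, no contrast is given for week 24, and a classical repeated-measures ANOVA would then need all three values.

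Four stronger readings are tempting but not supported:

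- **A mixed model would cure dropout bias.** It would not: it still excludes women lost before week 12 and removes only part of the shift when leaving depends on the change itself.
- **Dropout would take the trial below its own minimum of 20.** The 20 to 30 in the sample-size section is a benchmark for confirmatory imaging studies, the same section also cites 12 per group, and no dropout rate is stated.
- **The group main effect, which averages in baseline and halves the effect, will serve as the treatment test.** Nothing says so; naming time as the within-subject factor points to the interaction.
- **Omitting the age stratum inflates false positives.** The simulation shows the opposite.

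**Conclusion.** The point holds as one of precision and of an unused visit, not of bias. The named ANOVA leaves 15% to 35% of the change-score variance unrecovered for ρ between 0.7 and 0.3. At ρ = 0.5, the detectable difference is 0.89 SD where about 0.77 SD is available from the same 42 women. Any age effect on outcome adds a further loss of power, and week 24 has no clear test. The sizes depend on the assumed correlation: the gain shrinks as ρ rises. The dropout concern is real because the article raises it, but its size is unknown and a change of model only partly answers it. Severity: should fix.

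**What to change.** For each of SAS, SDS, SRSS, AFC, FSH and AMH, replace the two-way ANOVA with a linear mixed model (available in SPSS as MIXED):

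- response: week-12 and week-24 values
- fixed effects: group, visit, group × visit, baseline value × visit, and age stratum (cut at 35)
- women analysed in their assigned arm, using every available post-baseline value
- report VA minus SA with its confidence interval at week 12 (main) and week 24

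Listing all six outcomes also settles whether the ovarian markers receive a between-group test. Correct the duplicate AFC row in Table 2 so that the week-24 measurement is unambiguous.

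The model keeps women with only one post-baseline value. For those lost before week 12, add a sensitivity analysis for informative dropout that includes them, for example multiple imputation with the SA mean shifted over a stated range.

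Cost: some extra programming, one or two degrees of freedom, and the work of the sensitivity analysis. No additional patients or visits are needed. The change should be made before outcome data are seen.
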